### Evaluation of adverse events

Safety parameters are evaluated for each rTMS stimulation. Information relating to the adverse event, date of onset, date of resolution, severity, treatment, outcome, seriousness, and relationship to rTMS will be described in the medical record and case report form. When the relationship to rTMS cannot be ruled out, follow-up observations will be performed as much as possible until recovery to normal conditions. The terms used to describe adverse events conform to those provided by the Medical Dictionary for Regulatory Activities/Japanese version (MedDRA/J): International Conference on Harmonization (ICH).

The safety evaluation parameters are as follows:

Adverse events, particularly headache, stimulation site pain, stimulation site discomfort, presence or absence of muscle contraction (evaluated each time rTMS is delivered).The presence or absence of suicidal ideation (a parameter related to suicide in HAMD-17) and YMRS score (evaluated each time during the acute treatment and observation periods).

The results of the safety evaluation parameters should be recorded on the case report each time they are evaluated.

The severity of each adverse event is defined as follows:

Mild: the condition in which the participant feels discomfort but does not interfere with daily life.Moderate: the condition that restricts the participant’s daily life and makes the participant feel uncomfortable.Severe: the condition wherein the participant is unable to work or perform daily activities.

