### Definition of terms

The terms of the endpoints of this study are defined as follows:

Response: A response will be defined as a decrease of ≥50% in the HAMD-17 score measured at week 0 during the acute treatment period or a total HAMD-17 score of ≤12.Remission: The presence of remission will be defined as a total HAMD-17 score of ≤7.Relapse/recurrence: When a participant experiences conditions that meet the diagnostic criteria for depressive, manic, or hypomanic episodes defined in the DSM-5 after remission, during the acute treatment period, such conditions will be defined as relapse/recurrence. Additionally, relapse will be defined as disease exacerbation within half a year of remission, and recurrence will be defined as disease exacerbation after more than half a year of remission.

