### Criteria for discontinuation of individual study participant

If the principal investigator, principal investigator, or sub-principal investigator determines that it is not feasible to continue research on an individual research subject for any of the following reasons, the research on that research subject will be terminated. With full consideration given to the ethical aspects of study subjects, information on observations and tests related to the primary and secondary endpoints will be collected after the point of discontinuation to the greatest extent possible.

Withdrawal of consent or request for withdrawal to participate by the study participants.It is revealed after enrollment that the eligibility criteria were not met.Suicidal ideation is exacerbated (HAMD-17 score for suicide, ≥3) and continuation of the study is considered unfavorable.The total YMRS score is ≥8.The occurrence of an adverse event makes it difficult to continue the study.Pregnancy.Significantly poor compliance (rTMS is performed 2 days or less in 2 consecutive weeks).Occurrence of a convulsive seizure.Relapse/recurrence during the observation period.Discontinuation of the entire study, andThe investigator considers it appropriate to discontinue the study for other reasons.

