### Definition of case classification

Eligible cases: the participants who meet all the inclusion criteria and do not meet any of the exclusion criteria.

Discontinued cases: the participants who discontinued the study according to the criteria of discontinuation of individual case.

Handling the data of discontinued cases or missing values:

Discontinued casesFor the FAS, the values measured until the discontinuation time will be used for evaluation irrespective of the discontinuation time. For the PPS, the discontinued cases will be treated as missing values if the participant discontinues the study <4 weeks from the start of the study. Measured values will be used if the participant discontinues the study >4 weeks after the start of the study.Missing valuesThe primary endpoint, the MADRS total score, will be analyzed using mixed-effects models for repeated measures (MMRM) including those patients who had some missing values. Moreover, sensitivity analyses will be performed using single imputation methods such as baseline observation carried forward (BOCF) that performs an evaluation by substituting values measured at baseline for missing values and last observation carried forward (LOCF) by substituting the last measured value prior to the missing values. As for multiple imputation, distributions are assumed for the missing values with different parameters of the distribution according to conditions such as treatment methods. Additionally, a supplementary complete case analysis will be performed with participants having no missing data during the period of acute phase treatment.The time (days) to relapse or recurrence during the observation period, a secondary endpoint, will be defined as the interval (days) from the first day of the observation period to the date when the relapse or recurrence was identified. If a patient had not come to hospital before week 28 of the observation period, two types of handling of data will be considered; one is that the relapse or recurrence date will be regarded as 7 days after the final evaluation date, and the other is that the observation will be treated as censored on the final evaluation date. If no relapse or recurrence is confirmed at 28 weeks, the observation will be treated as censored on the day of 28 weeks.

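### Discontinuation for YMRS ≥8 is not tied to the relapse definition, so manic-pole relapses can be informatively censored in the secondary relapse analyses

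*Protocol article*

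**What the plan says.** All references are to the protocol article.

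- **Definition of terms.** Relapse/recurrence is the occurrence, after remission, of "conditions that meet the diagnostic criteria for depressive, manic, or hypomanic episodes defined in the DSM-5". No YMRS score enters the definition.
- **Criteria for discontinuation of individual study participant.** Two separate entries in the list are "The total YMRS score is ≥8" and "Relapse/recurrence during the observation period". The first requires no DSM-5 diagnosis. The list applies when an investigator "determines that it is not feasible to continue research on an individual research subject". The same section says that "information on observations and tests related to the primary and secondary endpoints will be collected after the point of discontinuation", as far as possible.
- **Evaluation of adverse events.** Suicidal ideation and YMRS are "evaluated each time during the acute treatment and observation periods", so YMRS is rated during the same months in which relapse is counted.
- **Definition of case classification, discontinued cases.** For the full analysis set (FAS), "the values measured until the discontinuation time will be used for evaluation irrespective of the discontinuation time".
- **Definition of case classification, missing values.** For time to relapse in a patient who had not attended up to week 28, two treatments will be considered. One dates a relapse 7 days after the last evaluation; "the other is that the observation will be treated as censored on the final evaluation date".
- **Secondary endpoints.** Relapse/recurrence rate and time to relapse or recurrence are both listed. Manic switch, measured by YMRS score, is listed separately. Time to relapse is analysed by Kaplan–Meier and log-rank in week-4 remitters, and a Cox model is also planned.

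**The concern.** Manic and hypomanic episodes are components of the relapse endpoint. Rising manic symptoms are also a reason to stop a patient, and the stopping criterion can be met before the episode is diagnosed. If such a patient is then censored, the reason for censoring is an early sign of the event being measured. Kaplan–Meier, log-rank and Cox analyses all assume that censored patients have the same future risk as those still followed, and here they would not.

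At stake is whether the relapse analyses cover both poles of the illness or mainly the depressive one. If active stimulation caused more switches than sham, censoring those patients would hide the excess and make maintenance of benefit look more similar between arms than it is.

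**Working it through.** **1. Reading the rules together.** Take a week-4 remitter in the observation period whose YMRS total reaches 8 without a DSM-5 episode at that visit, and whom the investigator discontinues.

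| Question | What the article says |
|---|---|
| Is this a relapse at that visit? | No; the definition needs a DSM-5 episode |
| Is the patient followed for relapse afterwards? | Yes, as far as possible (discontinuation criteria) |
| Is a later DSM-5 episode used? | Read literally, no: the FAS uses values up to discontinuation |
| Event or censored in time to relapse? | Either, if the rule for patients not seen to week 28 applies; neither is named as main |
| Does that rule cover investigator discontinuations? | Not stated; it is worded for patients who did not attend |

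The rules pull in different directions, and at least one route through them censors the patient at the last evaluation.

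**2. The plan's own figures.** The article gives no expected relapse rate and no expected frequency of YMRS ≥8, so there is no figure to reproduce for this endpoint. The stated 38 analysed and 48 consented per group do reproduce from an effect size of 0.65, two-sided 5% alpha, 80% power (normal approximation) and division by 0.80. They concern the MADRS endpoint only.

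**3. Illustration on assumed rates.** Assumptions, none from the documents:

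- 28-week depressive relapse d = 0.30 in both arms;
- cumulative YMRS ≥8 exits m;
- independent constant hazards;
- a share q of exits that would become DSM-5 episodes.

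The cumulative relapse estimate with a share q counted is 1 − (1 − d)(1 − m)^q. With all exits censored it is d.

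For m = 0.10:

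- all exits counted (q = 1): 1 − 0.70 × 0.90 = 0.370
- half become episodes (q = 0.5): 1 − 0.70 × √0.90 = 1 − 0.70 × 0.9487 = 0.336
- exits censored: 0.300

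Over a range of m:

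| YMRS exits m | Censored | Half become episodes | All counted |
|---|---|---|---|
| 5% | 30.0% | 31.8% | 33.5% |
| 10% | 30.0% | 33.6% | 37.0% |
| 20% | 30.0% | 37.4% | 44.0% |

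Within one arm, counting every exit and censoring every exit differ by 3.5 to 14 percentage points.

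**4. Between arms.** With exits of 10% active and 0% sham, the sham estimate is 30% throughout. The comparison is 37% against 30% (all counted), 33.6% against 30% (half) or 30% against 30% (censored).

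**5. Crude relapse rate.** If exits are simply recorded as no relapse, the active rate is the chance that depressive relapse comes first. The hazards are −ln 0.70 = 0.3567 and −ln 0.90 = 0.1054, giving 0.37 × 0.3567/(0.3567 + 0.1054) = 0.286. That is 28.6% against 30%, slightly in favour of active.

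**The case against.** A reader might infer that the plan removes manic-pole relapses from the endpoint and so is biased towards active stimulation. The documents do not support that, for these reasons:

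- A patient who already meets DSM-5 criteria at the visit with the raised YMRS has relapsed by definition. The two discontinuation reasons are not mutually exclusive.
- Discontinuation rests on an investigator's determination. YMRS ≥8 is not written as an automatic exit.
- Endpoint data are to be collected after discontinuation, so a later episode can be observed. The FAS sentence might also be read as only guaranteeing that early data are kept, although its literal sense is that data stop at discontinuation.
- One of the two treatments for patients not seen to week 28 counts an event. If that rule does not cover investigator discontinuations, no censoring is specified for them either.
- Manic switch is a secondary endpoint of its own, so the signal is reported elsewhere.
- Stimulation ends after 4 weeks plus a 3-week taper, and the log-rank analysis covers only week-4 remitters. Any excess of switches would bear on a subset, mostly after stimulation has stopped.

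It can also be said that censoring codes by discontinuation reason belong in a statistical analysis plan, which is not at hand.

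These arguments defeat the claim of certain removal and of a fixed direction of bias. They do not defeat the narrower point. The article does set rules here: it collects data after discontinuation but uses values only up to it, and it leaves two opposite treatments without a main one. Reporting manic switch separately does not correct the relapse estimates. The 7-day rule is no targeted remedy, because it would count any such early leaver as relapsed, whatever the reason.

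**Conclusion.** The point holds in a limited form. Following the article's text can censor patients on a symptom that foreshadows one component of the endpoint, and can leave unused the follow-up data that would resolve their status. It does not follow that every manic-pole relapse is lost. The bias would favour active stimulation only if active stimulation causes more switches, which the documents do not establish.

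Under the assumed rates, the between-arm difference ranges from 0 to 7 percentage points depending only on how exits are coded, with 3.6 points if half would become DSM-5 episodes. These figures rest on invented incidences and independent constant hazards; they show sensitivity to coding and are not a forecast.

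The affected outcomes are the secondary relapse rate and time to relapse. The primary MADRS comparison and the sample size are untouched. This should be corrected, but it does not threaten the trial's main conclusion.

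**What to change.** Reconcile the definition of relapse, the discontinuation criteria and the handling of discontinued and missing cases. The YMRS threshold and the stopping rule are left as they are; no view is taken on them.

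1. Keep the DSM-5 definition as the main relapse endpoint.
2. Record DSM-5 episode status at the visit where YMRS reaches 8 or more.
3. State that endpoint data collected after discontinuation are used in the relapse rate and time-to-relapse analyses, and amend the FAS rule accordingly for these endpoints.
4. State whether the two treatments for patients not seen to week 28 apply to investigator discontinuations, and name the main one.
5. Add a sensitivity analysis in which discontinuation for YMRS ≥8 in the observation period is an event on the date of that rating.

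The cost is a few sentences of endpoint and analysis wording, plus one DSM-5 status item at the visit concerned. YMRS is already recorded on the case report, and follow-up after discontinuation is already planned. No interim analysis is planned, so the rule can be settled before unblinding. The downside is that some events in the sensitivity analysis will be subsyndromal; the main DSM-5 analysis shows how much that matters.

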### Explanation of the terms

1. Hamilton’s Rating Scale for Depression (HAM-D).

This is a depression rating scale that was developed by Hamilton (24) and is used for measuring the severity of depressive symptoms in patients diagnosed with depression. The scale consists of a total of 21 parameters regarding depressive symptoms such as depressed mood or diminished interest and was confirmed to have clinical appropriateness and credibility by Hamilton (25).

2. Montgomery–Åsberg Depression Rating Scale (MADRS).

Montgomery and Åsberg developed the Comprehensive Psychopathological Rating Scale (CPRS) in Sweden, and the MADRS is a subscale of the CPRS, from which 10 parameters were extracted to evaluate depressive symptoms. This study used “the clinical evaluation of depression with the Japanese version of MADRS according to the Structured Interview Guide for MADRS (SIGMA)” (17).

3. Clinical Evaluation of Manic Disorders by the Japanese version of the YMRS.

This is a rating scale developed by Young et al. (20) for the clinical evaluation of manic episodes of mood disorders. The scale consists of 11 parameters related to manic episodes such as elevated mood and quantitative/qualitative increase in activity and has been confirmed to have sufficient credibility and clinical appropriateness.

4. Clinical Global Impression (CGI) (19).

This is a seven-stage clinical rating scale to evaluate the overall clinical impression.

5. Brief Assessment of Cognition in Schizophrenia, Japanese version (BACS-J).

This was developed by Keefe et al. (26) and comprises six tests of verbal memory, working memory, motor function, attention, verbal fluency, and executive function. The Japanese version was standardized in 2013 by Kaneda et al. (22).

6. THINC-it.

THINC-it is a screening tool developed to evaluate the cognitive function of patients with depressive episodes (23).

7. PHQ-9.

PHQ-9 is a self-completed rating scale developed to perform screening of depression, comprising nine parameters with four options. The Japanese version was examined for its translation, credibility, and appropriateness by Muramatsu (18).

8. EQ-5D (21).

EQ-5D is a self-completed rating scale developed to measure health-related QOL, comprising five parameters and three options.

### Case report form

All data will be entered into the Electronic Data Capture system (HOPE eACReSS). This system is compatible with the GCP requirements and allows for storage of the audit trail. The CRFs will not bear personal identifiable data including the participant’s name. Trial identification number will be used for identification. The study site will maintain a master participant identification log.

### Inspection of the source materials

Based on the descriptions in the protocol and separately prepared consent form, the physician representing this study, investigator, and head of medical institution where the study is conducted will be able to directly inspect all records related to this clinical study, including the source materials, at the time of monitoring and audit, as well as inspections conducted by the institutional review board and regulatory authority.

### Outcomes

#### Primary endpoint

The change in the MADRS total score from week 0 (starting point of rTMS) to week 4 will be used as the primary endpoint to clarify the treatment efficacy of rTMS in patients with bipolar disorder.

#### Secondary endpoints

The secondary endpoints will be as follows:

Response/remission maintenance rate during the observation period.Relapse/recurrence rate during the observation period.The time to relapse or recurrence during the observation period from the time origin is defined as end of the acute treatment.The change in scores of the MADRS, HAMD-17, Patient Health Questionnaire-9 (PHQ-9) (18), Clinical Global Impression (CGI) (19), Young Mania Rating Scale (YMRS) (20), EuroQol 5 Dimensions (EQ-5D) (21), Brief Assessment of Cognition in Schizophrenia Japanese version (BACS-J) (22), and THINC-integrated tool (THINC-it) (23) during the acute treatment and observation periods.Adverse events, particularly headache, pain at the stimulation site, discomfort at the stimulation site, and muscle contraction on stimulation.Suicidal ideation (suicide subscale score of HAMD-17) and manic switch (YMRS score).

### Criteria for discontinuation of individual study participant

If the principal investigator, principal investigator, or sub-principal investigator determines that it is not feasible to continue research on an individual research subject for any of the following reasons, the research on that research subject will be terminated. With full consideration given to the ethical aspects of study subjects, information on observations and tests related to the primary and secondary endpoints will be collected after the point of discontinuation to the greatest extent possible.

Withdrawal of consent or request for withdrawal to participate by the study participants.It is revealed after enrollment that the eligibility criteria were not met.Suicidal ideation is exacerbated (HAMD-17 score for suicide, ≥3) and continuation of the study is considered unfavorable.The total YMRS score is ≥8.The occurrence of an adverse event makes it difficult to continue the study.Pregnancy.Significantly poor compliance (rTMS is performed 2 days or less in 2 consecutive weeks).Occurrence of a convulsive seizure.Relapse/recurrence during the observation period.Discontinuation of the entire study, andThe investigator considers it appropriate to discontinue the study for other reasons.

### Statistical analysis

Statistical analysis will be conducted using the Statistical Analysis System software. All statistical tests will be two-sided, and the significance level will be set at 0.05. The primary analysis set of the efficacy and safety is the full analysis set (FAS), which will consist of all the randomized patients except those in whom neither active nor sham stimulation was performed. The secondary analysis set is the per protocol set (PPS), which will consist of all the eligible cases defined below.

### Definition of case classification

Eligible cases: the participants who meet all the inclusion criteria and do not meet any of the exclusion criteria.

Discontinued cases: the participants who discontinued the study according to the criteria of discontinuation of individual case.

Handling the data of discontinued cases or missing values:

Discontinued casesFor the FAS, the values measured until the discontinuation time will be used for evaluation irrespective of the discontinuation time. For the PPS, the discontinued cases will be treated as missing values if the participant discontinues the study <4 weeks from the start of the study. Measured values will be used if the participant discontinues the study >4 weeks after the start of the study.Missing valuesThe primary endpoint, the MADRS total score, will be analyzed using mixed-effects models for repeated measures (MMRM) including those patients who had some missing values. Moreover, sensitivity analyses will be performed using single imputation methods such as baseline observation carried forward (BOCF) that performs an evaluation by substituting values measured at baseline for missing values and last observation carried forward (LOCF) by substituting the last measured value prior to the missing values. As for multiple imputation, distributions are assumed for the missing values with different parameters of the distribution according to conditions such as treatment methods. Additionally, a supplementary complete case analysis will be performed with participants having no missing data during the period of acute phase treatment.The time (days) to relapse or recurrence during the observation period, a secondary endpoint, will be defined as the interval (days) from the first day of the observation period to the date when the relapse or recurrence was identified. If a patient had not come to hospital before week 28 of the observation period, two types of handling of data will be considered; one is that the relapse or recurrence date will be regarded as 7 days after the final evaluation date, and the other is that the observation will be treated as censored on the final evaluation date. If no relapse or recurrence is confirmed at 28 weeks, the observation will be treated as censored on the day of 28 weeks.

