### Number of participants

Number of participants who obtained consent: active stimulation group, 48; sham stimulation group, 48; total, 96 (1:1 randomization).

Number of participants analyzed: active stimulation group, 38; sham stimulation group, 38; total, 76 (1:1 randomization).

A meta-analysis performed by McGirr et al. included patients with a depressive episode of bipolar disorder, and the effect size in the amount of change in depressive symptoms was 0.48 for low-frequency stimulation to the right prefrontal cortex (9). Since there were no previous studies on concomitant pharmacotherapy in bipolar disorder, the effect size was estimated as 0.65 based on the results of the aforementioned meta-analysis. The sample size was estimated assuming the effect size of 0.65, two-sided alpha equal 0.05, and power of 0.80. Overall, 80% of participants will be considered appropriate to be included in the double-blind study according to the inclusion and exclusion criteria. Therefore, with the sample size multiplied by 1/(1–0.20), the number of participants who will need to provide consent is 48 for each group; thus, we will need to recruit 96 participants.

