### Analytical method

#### Primary endpoints

The change in MADRS total scores from weeks 0 to 4 during the acute treatment period will be analyzed using MMRM, in which the MADRS total score at week 0 as well as the interaction between the total score at week 0 and time point as continuous covariates (fixed effects), and the intervention, age, diagnosis, institution, time point, and interaction between the intervention and time point as categorical variables (fixed effects), and the response variables included will be the change in MADRS total scores measured at weeks 2 and 4. An unstructured covariance model will be fitted to intra-individual covariance structure, and Kenward–Roger degrees-of-freedom (DF) method will be applied to estimate the DF. The hypothesis test will be performed based on the least square estimates. Main comparison between the interventions will be performed by contrast at 4 weeks. As sensitivity analyses, analysis of covariance (ANCOVA) after LOFC, after BOCF for missing data at 4 weeks, and complete case ANCOVA will be performed. As secondary analyses, the change in the MADRS total score from weeks 0 to 4 will be analyzed using Wilcoxon rank-sum test. Interim analysis will not be performed.

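### Endpoint scores are to be collected after discontinuation, but the FAS rule stops at discontinuation and no stated analysis uses the later scores

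*Protocol article*

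**What the plan says.** Four parts of the protocol article bear on this.

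- **Criteria for discontinuation of individual study participant.** After a patient is discontinued, "information on observations and tests related to the primary and secondary endpoints will be collected after the point of discontinuation to the greatest extent possible". The listed reasons include worsened suicidal ideation, a YMRS total of 8 or more, adverse events, seizure and poor compliance.
- **Definition of case classification, discontinued cases.** For the FAS, "the values measured until the discontinuation time will be used for evaluation irrespective of the discontinuation time". For the PPS, patients who stop before 4 weeks are treated as missing.
- **Statistical analysis.** The FAS is the primary set. It holds every randomized patient who received any active or sham stimulation.
- **Analytical method, Primary endpoints.** The MMRM takes the MADRS changes at weeks 2 and 4 as responses and week 0 as a covariate. The test is the week-4 contrast. On robustness: "As sensitivity analyses, analysis of covariance (ANCOVA) after LOFC, after BOCF for missing data at 4 weeks, and complete case ANCOVA will be performed".

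The missing-values text under Definition of case classification also sketches a multiple imputation whose distribution parameters may differ by conditions such as treatment. The Analytical method list does not repeat it.

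**The concern.** One section has sites gather scores that another section, on its plain reading, tells the analyst not to use. Two groups of patients are affected in the primary test: those stopped between weeks 2 and 4, whose week-4 score is modelled rather than read, and those stopped before week 2, who are FAS members in name only.

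The MMRM is valid for these patients only if, given baseline, week 2 and the other model terms, their unseen scores behave like those of similar patients who stayed. Worsened suicidality, a raised YMRS and adverse events relate to outcome and possibly to active stimulation. The suicide item and the YMRS are checked at each rTMS delivery, so a stop can fall between MADRS visits with no warning in the earlier scores. This is where missing at random is least secure and where an observed score would be most useful.

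**Working it through.** **1. What the cut-off does, by time of stopping**

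| Stop | MADRS left after the cut | Role in the primary MMRM |
|---|---|---|
| Before week 2 | Week 0 only, a covariate | No response value, so no contribution to the likelihood |
| Between weeks 2 and 4 | Weeks 0 and 2 | Week 4 handled as missing at random, even if later measured |
| After week 4 | Weeks 0, 2 and 4 | Primary endpoint unaffected |

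Not every reason reaches the first row: the poor-compliance rule needs two consecutive weeks, so it cannot stop a patient before week 2.

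**2. The plan's own sample size**

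Input: "The sample size was estimated assuming the effect size of 0.65, two-sided alpha equal 0.05, and power of 0.80". Normal approximation: n = 2 × (1.960 + 0.842)² / 0.65² = 37.2, so 38 per arm, as stated. Then 38 / 0.80 = 47.5, so 48 per arm consenting, also as stated. No stated figure is wrong. With a t test, 38 per arm gives 79.9% power.

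The 20% allowance covers ineligibility after consent: "Overall, 80% of participants will be considered appropriate to be included in the double-blind study according to the inclusion and exclusion criteria". It leaves nothing for losses after randomization.

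**3. Power if early stoppers leave the model**

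The article gives no discontinuation rate, so the shares are assumptions, equal in both arms. Two-sample t power at effect 0.65:

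| Stopped before week 2 | Contributing per arm | Power |
|---|---|---|
| 0% | 38 | 79.9% |
| 5% | 36 | 77.6% |
| 10% | 34 | 75.2% |
| 15% | 32 | 72.6% |
| 20% | 30 | 69.7% |

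**4. How far apart the two rules aim**

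Let p be the share of active patients who stop before week 4 and r the share of benefit that they keep. With all week-4 scores used, effect = 0.65 × (1 − p) + 0.65 × r × p.

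| p | r = 0.5 | r = 0 |
|---|---|---|
| 5% | 0.634 | 0.618 |
| 10% | 0.618 | 0.585 |
| 15% | 0.601 | 0.553 |
| 20% | 0.585 | 0.520 |

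The gap from 0.65 is about 0.02 to 0.13 SD.

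A two-visit simulation agrees (38 per arm, 4,000 runs, correlation 0.6, half of the stops before week 2). At 20% stopping with r = 0, the cut-off estimate averaged 0.658 and the all-scores estimate 0.526, with about 68 of 76 patients contributing to the cut-off model. Stops were generated independently of outcome, so this shows two different targets. It does not show bias.

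**5. Do the listed sensitivity analyses react?**

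BOCF does. Assume 12% of active and 5% of sham stop, SD 10 (so 0.65 is 6.5 points) and active improvement of 8 to 15 points:

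- 8 points: 0.88 × 8 − 0.95 × 1.5 = 5.6, a shift of 0.9.
- 15 points: 0.88 × 15 − 0.95 × 8.5 = 5.1, a shift of 1.4.

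BOCF therefore keeps early stoppers and moves when active patients stop more often. It does so by assigning zero improvement, not by using a score. LOCF also substitutes an earlier value, and complete case drops these patients.

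**The case against.** **The cut-off is partly inferred.** The FAS sentence does not say in words that later values are excluded. It may be meant only to contrast with the PPS, by keeping partial data whenever the patient stops. That is possible, but an analyst following the sentence would stop at discontinuation, so it needs clarifying either way.

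**It may be a choice of target.** Estimating the effect had stimulation continued is legitimate, and follow-up scores can serve safety and secondary endpoints. This stands: the two sections are not logically incompatible. The article does not state that target, however, and gives the later MADRS scores no role in any analysis.

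**A reader might infer that the primary result is biased in favour of active stimulation.** The article does not support that. With 12% against 5% stopping and scores 5 to 10 points worse than modelled, the bias would be 0.07 × 5 = 0.35 to 0.07 × 10 = 0.70 points. That is 0.15 to 0.31 of a standard error of 10 × √(2/38) = 2.3. Those rates are invented. The direction depends on which arm stops more and why, and a patient stopped for a raised YMRS could have a low MADRS.

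**A reader might also infer that the sensitivity analyses are blind to the problem, or that LOCF and BOCF should go.** Neither follows. BOCF reacts, as shown, and the sketched multiple imputation can depart from missing at random. Removing BOCF would lose the one analysis in the Analytical method list that keeps every early stopper.

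**Conclusion.** The point holds as a gap between data collection and analysis. Endpoint scores gathered after discontinuation have no stated use, so the primary MMRM may model week-4 values that exist and gets nothing from patients stopped before week 2. Missing at random is doubtful for these patients, and the existing checks address that only partly, with imputed rather than observed values.

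The size cannot be fixed from the article. Under the assumed 5–20% discontinuation with half to all of the benefit lost, the two rules aim at effects about 0.02 to 0.13 SD apart. Each further 5% of an arm lost before week 2 costs about 2 to 3 points of power. The article does not show that the primary estimate is biased in a known direction, and the trial's validity is not in question. This is an inexpensive improvement worth making.

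**What to change.** 1. In Definition of case classification and in Analytical method, state whether week-2 and week-4 MADRS scores obtained after discontinuation enter the primary FAS MMRM, and which effect is targeted. Say also how FAS patients with no week-2 or week-4 value are handled.
2. Pre-specify an MMRM on all collected week-2 and week-4 values regardless of discontinuation, except where consent to data use is withdrawn. Make it the primary analysis or, at minimum, a sensitivity analysis, with the cut-off version as its counterpart.
3. Add the multiple imputation already sketched to the sensitivity list in Analytical method. LOCF and BOCF may stay.

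**Cost.** A change of wording and a little more analysis, since collection of the scores is already planned. The all-collected-data estimate may be smaller (0.52 to 0.63 SD under the assumptions above). If it becomes primary, t-test power at 38 per arm would be about 61% to 78% over the same range, so that choice is the sponsor's to weigh. As a sensitivity analysis it leaves the planned power unchanged. The article reports recruitment as ongoing and unblinding only after data fixation, so the change can still be made without knowledge of results.
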